## Abstract

Women confronted with recurrent pregnancy loss (RPL) are often desperately searching for a possible explanation and hoping they will someday fulfill a healthy pregnancy. Unfortunately, in more than 50% of these women no cause for their losses can be identified after clinical investigations and therefore clinicians have no treatment options to help these women. Although adaptations in several systems such as the metabolic, the cardiovascular, and the immune system are highly important to support early pregnancy, especially the contribution of a specific subset of immune cells in the uterus known as CD56^bright^ Natural Killer (NK) cells has gained a lot of interest, investigating separate RPL associated factors might not be the way forward. Moreover, a readily available and non-invasive exercise intervention might optimize all systems simultaneously, reducing metabolic, cardiovascular and immunological risk factors contributing to RPL. Therefore, we propose an aerobe exercise intervention and study the influence on the cardiovascular, the metabolic, and the immune system, with a particular focus on endometrial CD56^bright^ NK cells, in women with unexplained RPL. In this exercise intervention study, women with unexplained RPL will receive two questionnaires to assess baseline characteristics. Moreover, they will receive (1) an immunological assessment (by sampling menstrual blood, peripheral blood and a vaginal swab) (2) an assessment of the cardiovascular system (by transvaginal ultrasound to assess uterine artery perfusion, by measuring hemodynamic and autonomic nerve system responses during a tilt test and by maximum stress test on a cycle ergometer) and (3) a metabolic assessment (by sampling peripheral blood, urine and by measuring body characteristics) before and after intervention. The intervention consists of 12-weeks moderate exercise training based on 50–65% of heart rate reserve. One year after the end of the intervention women will receive a final questionnaire regarding possible subsequent pregnancy outcome. This clinical trial with a multi-systemic approach can not only provide new insights by studying contribution and associations of the immune system, the cardiovascular system and the metabolic system in women with unexplained RPL, it also can support shared decision-making between clinicians and patients by evaluating the importance of a ready available exercise intervention strategy.

## Introduction

Recurrent Pregnancy Loss (RPL), a distressing pregnancy complication defined as two or more losses before 24 weeks of gestation, nowadays affects 1–2% of all couples trying to conceive (1). Etiologies of explained recurrent pregnancy loss can roughly be classified in embryogenic (chromosomal abnormalities in the conceptus), maternal (antiphospholipid syndrome, thyroid malfunction, anatomical uterine anomalies), and paternal (lifestyle, sperm DNA fragmentation) (1). Sadly, in at least 50% of these couples, no underlying deficit is found which leaves clinicians without means to improve their pregnancy outcome (2). It has been suggested that non-receptive adjustments of different maternal systems, such as the metabolic system (3, 4), the cardiovascular system (5, 6) and the immune system (7–9), underlie a proportion of these unexplained pregnancy losses, as all these systems need to adapt properly for early pregnancy to be successful.

During early pregnancy, the maternal metabolic system needs to undergo changes toward an anabolic state for the increasing energy demand of the developing embryo (10). In addition, the maternal cardiovascular system needs to undergo systemic hemodynamic changes and local changes in uterine artery blood flow to ensure an increasing systemic blood supply to support both the developing embryo and placenta (11, 12). As for the immune system, the composition of the uterine immune cell population is truly unique since it has to tolerate the presence of a semi-allogenic fetus, while at the same time providing sufficient immunity to infectious uterine threats (13, 14). Hereby playing a fundamental role in early pregnancy.

In the uterus, the abundance of a specific immune cell population rapidly increases in the endometrium during the mid-secretory phase of the menstrual cycle and even up to 70% in de decidua during early pregnancy (15). This population of uterine Natural Killer (NK) cells is characterized by high levels of CD56 thereby also called CD56^bright^ NK cells, in contrast to the NK cell population in peripheral blood that mainly consists of CD56^dim^ NK cells (16). It is commonly thought that these CD56^bright^ uterine NK cells have an immunomodulatory function with the ability to secrete anti-inflammatory and growth factors, hereby playing a crucial role in embryo implantation by regulating adequate trophoblast invasion and remodeling of spiral arteries in order to establish proper early placentation (17). Early pregnancy safe harvesting of human CD56^bright^ uterine NK cells without endangering ongoing pregnancy is hardly feasible, however in non-pregnant endometrium it is possible to obtain samples through biopsies. Nevertheless, biopsies from endometrial tissue are invasive and painful, limiting their use for research purposes. Instead of biopsies, endometrial NK (eNK) cells can be easily isolated from menstrual blood and have shown to have the same phenotype as cells isolated from biopsies even allowing for collection of ∼10 times more lymphocytes than biopsies (18, 19).

As the metabolic, the cardiovascular and the immune system seemingly play a major role in sustaining successful pregnancy, research in these various systems has gained interest for pregnancy complications such as RPL. Women with RPL have been shown to have an increased incidence of metabolic disorders such as hyperhomocysteinemia, altered amino acid metabolism and an increased risk for developing the metabolic syndrome (3, 20, 21). Moreover, in women with RPL, several studies have found cardiovascular aberrations (22), amongst reduced circulatory plasma volume, reduced uteroplacental perfusion, increased total peripheral resistance, and hypertension (5, 23–25), also increasing their risk for cardiovascular diseases later in life (26, 27). In addition, alterations in uterine NK cell function and phenotype in patients with RPL have also been observed. Lower numbers of the CD56^bright^ NK cell subset and increased numbers of the CD56^dim^ NK cell subset with high expression of the activating CD16 receptor were found in the endometrium and decidua of women with RPL compared to controls without a history of RPL (9, 28–30). Furthermore, enhanced secretion of the pro-inflammatory cytokines IFN-γ and TNF-α by uterine NK cells was found in women with RPL compared to women with a previous normal pregnancy (31).

Although these prior studies emphasize the contribution of the cardiovascular, metabolic and immune system in relation to RPL, no study to date has looked at the added value of interplay between these different systems. Even taking into consideration the importance of a common regulator of these various systems; the sympathetic nervous system (32). Sympathetic hyperactivity has been linked to both cardiovascular and metabolic disorders and sympathetic dysfunction has been a significant contributor to the pathophysiology of immune mediated inflammatory diseases (33–35). Valuable work to develop effective therapeutic strategies for reversal of pathological sympathetic hyperactivity (36) is ongoing, nevertheless emerging evidence from recent animal and human studies seems to highlight the importance of exercise training as a widely prescribed non-pharmacological therapeutic strategy (37–39).

Nowadays, it is becoming generally accepted that exercise is associated with beneficial effects on the cardiovascular and metabolic system and even short workouts modulate immune responses that may have clinical impact (40). More notably, exercise is known to promote healthy reproduction by reducing the risk on pregnancy complications such as preeclampsia and gestational diabetes (41). For women with RPL specifically, inconclusive effects have been found and to date no studies investigate the impact of exercise on the chance of a live birth for RPL women (1, 41). Moreover, the effect of exercise on CD56^bright^ eNK cells has never been studied although it has been found that NK cells in the periphery are the most responsive immune cells to exercise, displaying an activation and acute mobilization to the circulation during physical exertion most pronounced during moderate training (42–44).

As a low number or altered function of CD56^bright^ eNK cells, in addition to the presence of metabolic and cardiovascular risk factors might contribute to RPL, we aim to gain new insights in the link between metabolic, cardiovascular and immune status of women with unexplained RPL with a unique multi-systemic approach and try to improve their overall health status with a moderate aerobe exercise intervention.

## Methods and analysis

### Study objectives and design

The aim of this multi-center interventional cohort study is to explore differences in immune parameters, in particular in CD56^bright^ eNK cells, and in cardiovascular, and metabolic parameters in women with RPL before and after an exercise intervention. Women referred to the department of Obstetrics and Gynecology of the Radboud University Medical Centre (RUMC) and the Maastricht University Medical Centre+ (MUMC+) for RPL will be included when no identifiable cause for their losses can be determined by clinical investigations.

According to current (inter)national guidelines of the European Society of Human Reproduction and Embryology (ESHRE), the clinical work-up includes; a standardized history from the couple, maternal screening for antiphospholipid antibodies (anticardiolipin, lupus anticoagulant and β2 glycoprotein I), maternal thyroid screening, assessment of anatomical uterine anomalies, paternal screening for sperm DNA fragmentation, and parental karyotyping if indicated (1).

After obtaining written informed consent, a questionnaire to assess general baseline characteristics and a short questionnaire to assess short health-enhancing physical activity (SQUASH) (45) will be conducted. Subsequently, peripheral blood and menstrual blood will be collected for assessment of the immune system and a vaginal swab will be collected to additionally evaluate the vaginal microbiome as the microbiome is known to play a fundamental role on the induction, training, and function of the immune system (46). Assessment of the cardiovascular system will be conducted by transvaginal ultrasound of both uterine arteries and by measuring hemodynamic responses during tilt test to determine hemodynamic parameters and sympathetic nervous system activity and responsiveness. Additionally, a maximum stress test on a cycle ergometer will be performed to determine the maximum rate of oxygen (VO_2_max) the subject’s body is able to use during exercise. Metabolic status will be assessed by measuring metabolic components in peripheral blood, urine and by measurements of body characteristics.

The intervention consists of a personalized 12-week heartrate-controlled cycle training program, that must be carried out on top of a subjects regular exercise regime and diet. Heart rate will be monitored by a Polar H10 heartrate monitor chest strap during cycle trainings. If women don’t want to participate in the training intervention, they will be asked to participate in a timeline-control group in which they receive similar questionnaires and assessments of their immune, cardiovascular and metabolic system. However, instead of an additional cycle training program of 12-weeks, they only follow their regular exercise regime and diet during an identical period. In this latter group, women will be included under similar criteria as the intervention group, preferably in a 1:1 ratio. Comparability between groups will be assessed on baseline characteristics prior to the intervention.

For both the intervention and control group, women will be asked to additionally donate menstrual blood at 4 and 8 weeks during the 12-week interval in order to assess intra menstrual cycle variation of eNK cells. Subsequently, all women will receive an identical immune, cardiovascular and metabolic assessment after 12 weeks and 1 year after intervention, a short questionnaire for monitoring subsequent pregnancy outcomes. See Figure 1 for a schematic overview of study design.

**FIGURE 1 F1:**
[figure not shown]
Schematic overview of study design.

#### Primary objective

To determine the changes in CD56^bright^ eNK cell number, phenotype and function before and after a moderate aerobe exercise intervention in women with unexplained RPL.

#### Secondary objectives

•To study baseline characteristics and baseline levels of physical activity in women with unexplained RPL.•To study immunological effects of an aerobe exercise intervention in women with unexplained RPL and compare these between endometrial and peripheral samples.•To compare immunological effects in women who undergo an aerobe exercise intervention and a timeline control group who do not follow an aerobe exercise intervention.•To evaluate additional effects of an aerobe exercise intervention on the vaginal microbiota (in relationship to eNK cell population) as it can influence the maternal immune system.•To evaluate additional effects of an aerobe exercise intervention on markers of cardiovascular and metabolic health that are known to be associated with adverse pregnancy outcomes in women with unexplained RPL.•To study additional effects of an aerobe exercise intervention on sympathetic nervous system activity, as the sympathetic autonomic system appears to be an important modulator of the immune system, the cardiovascular system, and the metabolic system.•To study additional effects of an aerobe exercise intervention on physical fitness levels measured by maximal oxygen consumption.•To monitor pregnancy outcome up to 1 year after an aerobe exercise intervention.•To investigate correlations between the immunological, cardiovascular and metabolic effects of an aerobe exercise intervention in women with unexplained RPL.

### Sample size

The effect of this interventional cohort study on CD56^bright^ eNK cells is hard to predict due to the novelty of this study using uterine NK cells as our primary objective. As for peripheral NK cells, a large meta-analysis showed an overall striking increase in cell count during moderate exercise training (186–344% of initial resting counts) (44). Since it is believed that training evokes redistribution of cells between blood and tissues due to increased hemodynamics (47), we hypothesize that moderate exercise possibly enables mobilization of NK cells to the endometrium and therefore affects CD56^bright^ eNK cell numbers. Moreover, after moderate exercise training, numbers of peripheral NK cells overall decreased to their initial NK cell count along with an analogous depression of cytolytic activity before complete recovery (44). Although at first these changes per training seem unlikely to have a major influence on general population health, it could be that a cumulative period of immune depression becomes of greater importance, especially to reproductive health. As these studies from this meta-analysis included around 20 subjects to show an effect on peripheral NK cells, we will aim to end up with around 20 women for data analysis. Furthermore, based on previous research showing discriminatory levels of the peripheral NK cell marker LILRB1 in two independent studygroups (8) we expect a detectable significant difference for a mean fluorescent intensity of 473 between group 1 (mean 771 ± 600) and group 2 (mean 298). When comparing two independent study groups for a continuous endpoint with an alpha of 0.05 and a beta of 0.2, a total number of 50 women, 25 in each group is needed to detect this difference of 600 and show discriminatory levels of NK cell markers. Additionally, we performed a pilot study to evaluate the feasibility of training women with RPL, to determine the modifiability of risk factors for RPL (evaluations of CD56^bright^ eNK cells were not part of this pilot study). We found that already after 1 month of supervised training, 9 out of 12 women significantly showed an improved VO_2_max (26.7 versus 27.4, *p* = 0.024) and one woman was unable to complete her trainings (unpublished data). Therefore, we expect that after a longer period of physical training at least 75% of the included women will improve their physical fitness (48).

In conclusion, we expect a clinically significant training-induced improvement with the inclusion of 30 women, assuming a similar effect on eNK cells as in peripheral blood. This allows for a drop-out rate of approximately 15%, leaving around 25 subjects for analysis hereby considering a compliance of 75% to the training intervention.

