On average, 30 new couples who experienced RPL visit our clinic every month, of which approximately 15 women have unexplained RPL. These women will be informed about the study by the health professionals in our clinic and a patient information folder will be handed out to women who are interested to read about the study in more detail. The health professional also asks for permission to pass their contact information to the study investigator. Within 1 week women will be contacted by the study investigator to get additional verbal information about the study and answer possible questions. During this consultation, the study investigator will ensure that all subjects will be given full and adequate verbal and written information about the nature, purpose, possible burdens and benefits of the study. Furthermore, it will be emphasized that participants are free to withdraw from the study at any time without specific reason. After eligibility is verified, women are free to take the time they need before deciding if they would like to participate or not. We estimate that monthly approximately 4 out of these 15 eligible women would like to participate in the intervention study. Additionally, we anticipate extra participants via RiNet (Reproductive Immunology network in the Netherlands)^1^ and via Freya (Dutch association for women with fertility problems).^2^ Information about the study and contact details will be provided on both websites. In this way, women who are interested in possible participation can contact the study investigator directly. Further course will be the same as for women who are informed about the study in the RPL clinic at MUMC+ or first trimester pregnancy clinic at the RUMC.

In our clinical experience we observed profound willingness in this specific patient group to participate in scientific studies which potentially help them and future patients. Our inclusion rate is however anticipated on the more modest side, because we do respect practical concerns, mainly related to time investment issues in couples who would like to conceive on short notice.

A total of 30 women with unexplained RPL will be included in this study to participate in the intervention group, additionally a maximum of 30 RPL women will be included under similar criteria in the timeline control group. Allocation was non-randomized as patients were allocated based on what was considered most appropriate for their individual circumstances.

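### The 25 women said to remain for analysis allow for drop-out only; the 75% compliance that the sentence claims to consider does not enter the number.

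*Protocol article*

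**What the plan says.** All the figures are in the Sample size section of the protocol article, apart from one restatement under Study population and recruitment.

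- **First target.** By analogy with the size of earlier exercise studies of peripheral NK cells: "we will aim to end up with around 20 women for data analysis".
- **Second target.** From a two-group calculation on the marker LILRB1, with "a mean fluorescent intensity of 473 between group 1 (mean 771 ± 600) and group 2 (mean 298": "a total number of 50 women, 25 in each group is needed to detect this difference of 600".
- **Pilot.** VO2max improved in 9 of 12 women after one month of supervised training, and one woman could not complete. From this the authors expect that "at least 75% of the included women will improve their physical fitness".
- **Conclusion of the section.** "we expect a clinically significant training-induced improvement with the inclusion of 30 women". The text then says "This allows for a drop-out rate of approximately 15" per cent, "leaving around 25 subjects for analysis hereby considering a compliance of 75% to the training intervention".
- **Restatement.** Study population and recruitment confirms that the 30 refers to one arm: "A total of 30 women with unexplained RPL will be included in this study to participate in the intervention group". At most 30 controls are added.

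**The concern.** The closing sentence gives two allowances, drop-out and compliance, and one resulting number. A reader will take the 25 as net of both, but it is net of drop-out only.

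What is at stake is which women the 25 describes. If they are women who complete and comply, 30 inclusions do not yield them. If they are simply women who complete, the sentence claims a margin for poor adherence that was never built in. The section also gives two evaluable targets, around 20 and 25 per group, without ranking them. About 19 compliant completers would roughly meet one and miss the other, so the reader cannot tell whether the planned size is adequate on the authors' own terms.

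**Working it through.** **Inputs, all from Sample size:** inclusion 30; drop-out about 15%; compliance 75%; stated number for analysis around 25; other aim around 20; two-group requirement 25 per group; difference 473, SD 600; alpha 0.05, beta 0.2. Sidedness is not stated; two-sided is assumed.

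**1. Reproduce the stated 25.**
- Forward: 30 x (1 - 0.15) = 25.5.
- Backward: 25 / 0.85 = 29.4, rounded up to 30.
- Drop-out alone reproduces the plan in both directions.

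**2. Try to bring compliance in.**
- Compliance instead of drop-out: 30 x 0.75 = 22.5.
- Compliance on top of drop-out: 30 x 0.85 x 0.75 = 19.1, about 19.
- Neither gives around 25.
- To keep 25 compliant completers: 25 / (0.85 x 0.75) = 39.2, so 40 inclusions. To keep 20: 20 / (0.85 x 0.75) = 31.4, so 32.

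**3. Locate the 25 per group.**
- Standardised difference: 473 / 600 = 0.788.
- n per group = 2 x (1.96 + 0.842)^2 / 0.788^2, which rounds up to 26 (27 with the t-test). This is within 2 of the stated 25.
- The sentence gives 600 as the difference to detect, but 600 with SD 600 would need only 16 per group (17 with the t-test). So the 25 corresponds to 473, with 600 as the SD.

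**4. What the change from 25 to 19 means for the primary, before-after objective.** The detectable standardised paired change at 80% power is approximately (t for 0.975 + t for 0.80, on n - 1 degrees of freedom) / sqrt(n).
- n = 25: (2.064 + 0.857) / 5 = 0.58 SD of the within-woman change.
- n = 19: (2.101 + 0.862) / 4.359 = 0.68 SD.
- The exact noncentral-t calculation gives 0.584 and 0.680.

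**5. The same change against the secondary two-group benchmark.** For a difference of 473 with SD 600, t-test power is 78% with 25 v 25, 72% with 19 v 25 and 66% with 19 v 19. These figures only place the 19 on the section's own scale. The 473 is a LILRB1 difference between two independent study groups and is not presented as a training effect.

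**6. The two values of 75%.** The pilot gives 9/12 = 75% of women with improved VO2max, which is a response rate. Compliance of 75% appears in the closing sentence without definition or source. The pilot's only figure near adherence is the one non-completer (11/12 = 92% completing, if she is one of the 12), which is not 75% either.

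**The case against.** The strongest reply is that 25 is not wrong. It follows from 15% drop-out, equals the two-group requirement and exceeds the aim of around 20. Compliance may be a per-woman measure, such as the share of sessions attended. The Intervention section has compliance followed woman by woman, through weekly heart-rate results and phone calls. On that reading nobody need be subtracted. Rules on analysing non-adherent women often sit in a full protocol or analysis plan that is not shown, and the Discussion calls the trial explorative.

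Most of this stands, and it limits the point. It does not rescue the wording: on the per-woman reading too, compliance contributes nothing to the 25, although the sentence says it was considered.

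A reader might infer four stronger things that the document does not support.

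- **That the 75% compliance was taken from the 9 of 12 VO2max responders.** The figures match and stand close together, but no text links them. This is an inference.
- **That 25 conflicts with the aim of around 20.** 25 is not a shortfall against 20, and 19 is close to 20. The two targets are unreconciled, not contradictory.
- **That power collapses because a quarter of women gain nothing.** Multiplying 473 by 0.75 gives a two-group power of about 54% with 25 per group. That rests on an assumed absence of benefit in 25% of women, applied to a marker difference not presented as a training effect. It is at most a labelled sensitivity figure.
- **That non-adherent women will be removed from one arm, biasing the comparison.** The article states no such exclusion.

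**Conclusion.** The point holds as a misstatement in the sample-size rationale. The 25 claims an allowance for compliance that it does not contain. If compliance is a further loss at the stated 75%, independent of drop-out, about 19 women remain instead of 25. The detectable paired change then rises from 0.58 to 0.68 SD (80% power, two-sided alpha 0.05). If compliance is a per-woman attendance measure and all completers are analysed, the 25 stands and only the claim to have considered compliance is empty. The article does not say which reading is meant, nor which of its two targets governs. This should be corrected, but it does not invalidate an exploratory study.

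**What to change.** In Sample size:

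1. Name one evaluable target and drop or subordinate the other.
2. State that the 25 allows for about 15% drop-out only. Then either delete the claim that it considers compliance, or give the compliant number (about 19) beside it.
3. If the 75% is kept, define compliance and give its source. The VO2max response rate cannot serve, because it measures response. Pilot completion cannot serve either: one non-completer after one month of supervised training speaks to drop-out, not to adherence over 12 weeks.
4. State that all women with menstrual samples before (T0) and after (T3) the intervention are analysed regardless of adherence, with the adherent subset as a supportive analysis.
5. Report the detectable paired change for each set: 0.58 SD with 25 and 0.68 SD with 19. Give any figure for a diluted effect only as a labelled sensitivity assumption.

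The cost is a few sentences. No patients or visits are added. The only drawback is that the stated figure becomes less favourable.
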